### Study setting

This trial will be conducted at the Hepatopancreatobiliary Surgery Institute of Gansu Province, located in Lanzhou City, Gansu Province, China. Affiliated with the First Hospital of Lanzhou University, this institute possesses professional expertise in the diagnosis and precision treatment of digestive system diseases, with particularly notable proficiency in the management of biliary tract diseases. An overview of the trial procedure is presented in Figure 1.

**Figure 1 fig1:**
[figure not shown]
Participant recruitment flow chart.

### Eligibility criteria

Our target population comprises patients whose electronic medical records revealed small gallstones (defined as gallstones with a diameter less than 2 mm) and who underwent gallbladder ultrasound examinations at this hospital.

Inclusion criteria. (1) Adult patients who were diagnosed with small gallbladder stones (maximum diameter < 2 mm) via ultrasound and had no prior treatment history. (2) Patients of either sex, aged between 18 and 70 years, who were willing to participate in this study.

The exclusion criteria were as follows: (1) age <18 years or >70 years. (2) History of endoscopic retrograde cholangiopancreatography [ERCP]. (3) Previous gallstone removal surgery with gallbladder preservation. (4) History of acute or chronic pancreatitis or cholangitis. (5) Mirizzi syndrome. (6) History of gastrointestinal surgery. (7) Gastrointestinal obstruction. (8) Dysfunction of the sphincter of Oddi. (9) Gallbladder neck polyps. (10) Abnormal gallbladder structure (e.g., the gallbladder has multiple folds). (11) Gallbladder mass. (12) Common bile duct stones, extrahepatic biliary tract stones, or active biliary tract infection. (13) Congenital biliary abnormalities. (14) Biliary injury or surgery. (15) Biliary tumors. (16) Gastrointestinal bleeding, liver cirrhosis, or other malignant diseases. (17) Significant arrhythmia, bradycardia, or atrioventricular block. (18) Severe hypertension or liver or kidney insufficiency. (19) Immune, endocrine, hematological, or mental disorders. (20) Severe cerebrovascular disease. (21) Allergy to relevant foods. (22) Pregnant or breastfeeding women. (23) Unwillingness or inability to consent to participate.

### Intervention description

Data pertaining to the small gallstones will be extracted from the electronic medical records of outpatients who underwent gallbladder ultrasound examination at this hospital. Follow-ups will be conducted via telephone. If a patient meets the inclusion and exclusion criteria, expresses willingness to participate, and has no clinical symptoms related to gallstones, a gallbladder ultrasound will be repeated by a trained and experienced sonographer. Only patients with gallstones measuring less than 2 mm at this follow-up examination will be eligible for enrollment. Eligible patients will be randomly assigned to the experimental group or the control group. The attending physician will explain the potential risks and benefits of the intervention, and written informed consent will be obtained from all participants.

The patients in the experimental group will take 50 mL of oral functional fatty acids on an empty stomach every morning for 6 consecutive days. In the control group, patients will first receive oral placebos for 3 days, followed by the same dose of oral functional fatty acids as the experimental group for the next 3 days. The blinded ultrasound physicians will perform gallbladder ultrasounds on the 3rd and 6th days after treatment to evaluate the effect of small gallstone expulsion. We chose the 3rd and 6th days after the intervention as the observation time points for evaluating the effect of small gallstone expulsion for the following reasons. On the basis of our experience and data from pilot studies, after 6 days of oral functional fatty acids, small gallstones were effectively expelled or exhibited a reduction in their content. However, it remains unclear whether the small gallstones were expelled precisely on the 6th day of intervention or before. Therefore, using the median value as a reference, we aimed to identify an optimal time point for evaluating the expulsion of small gallstones. Well-trained volunteers will follow up with patients during treatment to increase patient compliance and facilitate timely recording and management of any complications.

The functional fatty acids are a proprietary edible oil blend manufactured by Seawit Qingdao Life Science Co., Ltd., China, consisting of 60% medium-chain triglycerides (MCT, predominantly caprylic acid C8:0 and capric acid C10:0) and 40% long-chain triglycerides (LCT, predominantly monounsaturated oleic acid C18:1 and polyunsaturated linoleic acid C18:2). The preparation has a pale yellow color, transparent texture, and light cucumber flavor.

The placebo was specifically formulated to match the functional fatty acids in color, transparency, flavor, and viscosity to maintain blinding integrity. It consists of purified water, 0.15% (w/v) xanthan gum to replicate the oily texture, and cucumber flavoring powder. Trial nurses will prepare the placebo fresh daily immediately before administration to ensure consistent sensory properties.

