**Table tab1:** 

Arms	Interventions
One functional fatty acids with a light fruity flavor	Dietary therapy method: Days 1–3: oral administration of functional fatty acids Days 4–6: oral administration of functional fatty acids
Placebo	Days 1–3: oral administration of placebo Days 4–6: oral administration of functional fatty acids

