### Allocation

Eligible candidates will be identified through a systematic medical record review and approached for participation via proxy contact. Study randomization will be managed by biostatisticians using a validated computer algorithm to generate a 1:1 allocation sequence, with 100 sequentially numbered sealed opaque envelopes independently encoded and securely stored in a tamper-evident repository.

After confirming that the inclusion criteria have been satisfied, two designated researchers will verify the patient’s identity. They will record the number of unopened envelopes before simultaneously opening the allocation document and signing it together. The trial nurse will administer the corresponding oral treatment protocol to the patient in accordance with their allocation number.

Both the functional fatty acids and the placebo were manufactured by (Seawit) Qingdao Life Science Co., Ltd., China.

Treatment assignments will be securely transmitted by an independent study team. Attending physicians will receive unique assignments for each patient only after all the preintervention protocols have been completed. These protocols include a comprehensive clinical evaluation, the collection of signed informed consent documents, and the confirmation of procedural readiness by the study team.

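### The listed placebo ingredients do not account for the claimed match to the oil, and the control arm's day-4 product change leaves participant blinding unsupported for later self-reported outcomes

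*Protocol article*

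**What the plan says.** Under Intervention description, the active product is introduced thus: "The functional fatty acids are a proprietary edible oil blend". It is 60% medium-chain and 40% long-chain triglycerides, and "The preparation has a pale yellow color, transparent texture, and light cucumber flavor". Of the placebo the same section says: "The placebo was specifically formulated to match the functional fatty acids in color, transparency, flavor, and viscosity to maintain blinding integrity". Its composition follows: "It consists of purified water, 0.15% (w/v) xanthan gum to replicate the oily texture, and cucumber flavoring powder".

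The unnumbered arms table that follows labels the active arm "One functional fatty acids with a light fruity flavor". It shows the experimental arm on the oil for all six days, and the control arm on placebo for days 1-3 and on the oil for days 4-6.

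On who makes the placebo, Intervention description says "Trial nurses will prepare the placebo fresh daily immediately before administration to ensure consistent sensory properties", while the Allocation section says "Both the functional fatty acids and the placebo were manufactured by (Seawit) Qingdao Life Science Co., Ltd., China".

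Trial design and Blinding both state that participants are blinded. Apart from emergencies, Trial design allows unblinding only at the analysis, once the trial is over; Blinding allows it only after the data are locked. Neither section qualifies the claim for the change of product on day 4.

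**The concern.** In an ordinary parallel-group trial each participant meets one product and has nothing to compare it with, so a moderate mismatch may go unnoticed. Here one arm meets both products on consecutive days. The quality of the match therefore matters more than usual, and the description of the match does not hold together.

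The outcomes at stake are those that depend on what the participant reports or chooses to do. Table 1 includes a self-rated pain score at 7 days and daily counts of nausea, vomiting and diarrhoea over 14 days. The Statistical analysis section lists a between-group comparison of adverse events among its key secondary analyses. Willingness to keep taking the product on days 4-6, and to return for the day-6 scan, could also depend on what participants believe they are taking.

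**Working it through.** The plan gives no figure for this point, so the check sets its statements side by side.

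**1. Does the ingredient list support the claimed match?**

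| Property claimed to match | Active product as described | What the placebo list offers |
|---|---|---|
| Colour | Pale yellow | No colouring named. The flavouring powder might tint it, but this is not stated. |
| Transparency | Transparent | Not addressed |
| Flavour | Cucumber in the text, fruity in the arms table | Cucumber powder, which fits the text and not the table |
| Viscosity and texture | Oil blend | Water with 0.15% xanthan gum as the thickener, and no oil |

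The list does not explain the colour. The flavour matches under only one of the two descriptions of the active product. The texture rests on a thickened aqueous drink standing in for an oil. The article reports no sensory test in either direction.

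**2. Who meets both products?**

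- Control arm: placebo on days 1-3, oil on days 4-6. Up to 50 of 50 meet both.
- Experimental arm: oil on days 1-6. None of 50 meets both.

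So up to 50 of 100 participants, half the trial, can compare directly. For someone who knows that only one arm switches, no change on day 4 is informative too. In principle the switch can then reveal the arm to participants on both sides (50 + 50 = 100).

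**3. Which outcomes fall after the switch?**

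- Day-3 complete expulsion (primary): before the switch, and read by sonographers blinded to group and to previous results.
- Day-6 complete expulsion (key secondary): after the switch, with the same blinded reading and a third reader for disagreements. Participants' knowledge could act here only through adherence or dropout.
- Pain score at 7 days: after the switch, whether the 7 days run from the first dose or from the last.
- Nausea, vomiting and diarrhoea over 14 days: counted from the first dose, 14 - 3 = 11 of the 14 days follow the placebo period; counted from the last dose, all 14 do.
- Bilirubin, gallbladder volume and wall thickness: after the switch, but not self-reported.

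**4. Who makes the placebo?** Allocation names the company and Intervention description names the trial nurses. Both can be true if the company supplies ingredients or a dry mix that the nurses make up. The article does not say so.

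**The case against.** A reader might infer that the placebo cannot match the oil, that controls will therefore identify their arm, and that the trial is not double-blind. The documents do not support that much.

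- The article states that the placebo was formulated to match. It is a condensed account, the powder may add colour, and there are no sensory data. What stands is that the listed ingredients do not account for the claimed match, not that a match is impossible.
- The flavour conflict is one phrase in a table label. The only full product description gives cucumber for both products. If the label is simply wrong, this part is a wording correction.
- The two statements about preparation can be compatible, so they do not show that the wrong product was matched. They need one clear account. Whether nurses who prepare the placebo can themselves be blinded is a separate question about staff.
- Inferring the arm requires noticing a change and knowing that only one arm switches. The consent pages are not shown, so what participants are told is unknown. This makes the conclusion conditional but does not remove it.
- A reader might also infer that the expulsion endpoints are biased. A day-4 change cannot affect a day-3 result, and blinded readers protect the image assessment at both time points.

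One consideration runs the other way. If an aqueous drink is recognisable as not being an oil, it may be recognised from the first dose. Days 1-3 therefore cannot simply be assumed to be well masked.

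**Conclusion.** The point holds in a limited form. As written, the placebo specification does not support the match claimed for it, and the arms table contradicts the text on the active product's flavour. With a product change in one arm only, the unqualified claim of participant blinding is not supported after day 4, and it is untested for days 1-3.

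Up to 50 controls have a direct comparison. The size and direction of any resulting bias cannot be worked out from the documents. The exposure is mainly to self-reported pain, nausea, vomiting and diarrhoea, and to adherence and retention on days 4-6. The two expulsion endpoints are much less exposed. The conclusion assumes that the ingredient list is substantially complete and that at least some participants know the design. It should be corrected, but it does not undermine the primary comparison.

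**What to change.** 1. Reconcile the product description and the arms table to one flavour for the active product.
2. Reconcile Intervention description and Allocation to one statement of who supplies the placebo and who prepares it.
3. Give the placebo's full composition, and correct it so that colour and flavour match the actual active product, for example with a food colouring.
4. Record each participant's treatment guess before the day-4 dose and again at day 6, and report the guesses by arm.
5. Amend Trial design and Blinding so that reliable participant blinding is not claimed for self-reported outcomes after the day-4 switch. Let the claim for days 1-3 rest on the guess taken before the day-4 dose.

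The cost is a wording amendment, a small change to the placebo recipe and one question asked twice. The double-blind claim becomes slightly less favourable. The allocation ratio, sample size and primary analysis do not change.

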The trial is being conducted at the First Hospital of Lanzhou University. The analysis will be based on intention-to-treat (ITT) and per-protocol (PP) methods. A minimum of 50 participants per group is needed to achieve 80% statistical power (with a two-sided *α* = 0.05) in detecting a clinically meaningful difference in the primary efficacy endpoint (e.g., the proportion of participants with complete gallstone expulsion within the treatment period). This sample size calculation is consistent with the superiority design, as it is powered to identify a significant between-group difference in favor of the experimental intervention.

Both participants and researchers will be blinded to the group assignments (double-blinding). The statistician conducting the analysis will remain unaware of the groupings, and the trial nurses will administer the oral treatment. Neither the participants nor the researchers will know which intervention each group receives. Unblinding will be permitted only at the time of statistical analysis, after the trial is completed. In case of an emergency (e.g., acute biliary obstruction), unblinding may be permitted to ensure participant safety. In such an event, the time, reason, and person responsible for the unblinding will be recorded promptly, and the trial monitor will be notified. Participants who are subject to unblinding will be excluded from the final efficacy analysis but will remain in the safety analysis.

In this study, gallstones with a diameter of less than 2 mm were selected as the target objects. The diameter of the cystic duct is generally approximately 2–3 mm, and the inner diameter of the common bile duct is 6–8 mm. Stones smaller than these ductal diameters have the anatomical feasibility to pass through. This selection not only allows the evaluation of gallstone expulsion in the early formation stage (where intervention may be most impactful) but also reduces the potential risk of biliary obstruction—an important safety consideration that aligns with the trial’s goal of assessing both efficacy (per superiority design) and safety.

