## Methods

### Primary objective

The primary aim of this study is to determine the effectiveness of oral functional fatty acids in facilitating the expulsion of small gallbladder stones. Upon trial conclusion and researcher and participant unblinding, the pre and postintervention ultrasound examination data will be meticulously analyzed to comprehensively compare the expulsion volume and expulsion rate of gallbladder stones between the experimental group and the control group on the third and sixth days after the intervention through in-depth intergroup comparisons. Moreover, we will perform a detailed analysis of the differences in the expulsion volume and expulsion rate of gallbladder stones within the experimental group to compare the outcomes after a six-day intervention with those after a three-day intervention; relevant data from the control group will be subjected to the same in-depth intergroup analysis.

We hypothesize that the stone expulsion rate among patients in the experimental group who will consume functional fatty acids for 3 days, will be significantly greater than that among patients in the control group who will take placebo over the same period. Additionally, we anticipate that the stone expulsion rate of the experimental group patients who will take functional fatty acids for 6 days will exceed that of the control group patients who will receive placebo supplemented with functional fatty acids. Furthermore, when the experimental group and the control group are compared, the volume of gallstones expelled and the expulsion rate following a six-day intervention are expected to be notably greater than those observed after a three-day intervention.

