### Blinding

Both participants and all study personnel involved in intervention administration, clinical assessment, ultrasound examination, and data collection will be blinded to group assignments (double-blinding). The statistician conducting the final data analysis will also remain unaware of group allocations throughout the analysis process. Unblinding will be permitted only after all data have been collected and locked for final statistical analysis.

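### Dosing staff are declared blinded, yet trial nurses mix the placebo just before it is given, so preparing a dose reveals the control arm on days 1–3

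*Protocol article*

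**What the plan says.** The protocol article makes a broad blinding claim. The Blinding section states: "Both participants and all study personnel involved in intervention administration, clinical assessment, ultrasound examination, and data collection will be blinded to group assignments". The Trial design section adds: "Neither the participants nor the researchers will know which intervention each group receives".

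The Trial design section also says who gives the product: "the trial nurses will administer the oral treatment". The Allocation section repeats that a trial nurse gives the treatment belonging to the participant's allocation number.

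The Intervention description gives the composition of both products. The active product is a proprietary blend of medium-chain and long-chain triglycerides made by a company. The placebo is purified water with 0.15% xanthan gum and a flavouring powder. On preparation it says: "Trial nurses will prepare the placebo fresh daily immediately before administration to ensure consistent sensory properties".

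The Allocation section describes the source of the placebo differently: "Both the functional fatty acids and the placebo were manufactured by" the company. The same section has two researchers record the unopened envelopes "before simultaneously opening the allocation document and signing it together", and has attending physicians receive an assignment for each patient.

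**The concern.** Blinding of the people who give a product depends on their not being able to tell which product they hold. Someone who stirs gum and flavouring into water can tell. The article assigns that task to the same category of staff that gives the dose, and it describes no separate preparer.

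Days 1–3 are the days on which the primary comparison rests. The Trial design section itself says that the day 6 comparison is between two durations of active treatment. A nurse who knows the arm in those first days could, without intending to, affect whether a dose is finished, what a participant mentions about pain, nausea or diarrhoea, and whether the participant stays in the trial. The secondary outcomes include a self-rated pain score and daily symptom counts, and adverse events are compared between groups.

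**Working it through.** No formula applies; the check is a comparison of sections.

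**Step 1: who must be blinded.** The Blinding section covers all personnel involved in administration.

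**Step 2: who administers.** Trial nurses, according to both Trial design and Allocation. They fall within step 1.

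**Step 3: who prepares the placebo.** Trial nurses, each day, directly before dosing (Intervention description).

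**Step 4: what preparation reveals.** The placebo is mixed from water, gum and powder, whereas the active product is a manufactured oil. No matching bedside preparation of the active product is described. The arm table gives placebo to the control arm only, on days 1–3 only. Mixing a placebo for a named participant therefore identifies that participant as a control. The knowledge does not vanish on day 4, when both arms move to the oil.

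**Step 5: does coding prevent this?** No. The envelopes are encoded and the nurse works from an allocation number, but the nurse must still know whether to mix a placebo for that number. The act of preparation breaks the code.

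**Step 6: which product source is meant?** There are three readings of Allocation set against Intervention description:

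| Reading | Consequence |
|---|---|
| The company delivers finished placebo | The sentence on nurse preparation is wrong; the blinding claim could stand |
| Nurses make the placebo from ingredients | The manufacture sentence and the blinding claim for dosing staff are wrong |
| The company supplies components that nurses make up | The two product sentences agree, but the blinding claim for dosing staff is still wrong |

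Under each reading at least one sentence must change.

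**Step 7: extent.** There are 50 planned controls with 3 placebo days each. At one preparation a day this is 50 × 3 = 150 preparations, each of which reveals an arm.

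**Step 8: what stays protected.** The standardized ultrasound protocol has two sonographers read independently, blinded to group and to previous examinations, with a third senior reader for disagreements. The Statistical analysis section adds a blinded adjudication committee. Nothing in steps 1–7 touches these safeguards.

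**The case against.** The strongest reply has four parts.

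*The preparer and the doser may be different nurses.* The article never says that they are one person, and the Quality assurance section refers to an operating procedure for administration that is not shown. This stands as an uncertainty. However, no separation is described, and a nurse who makes up a dose immediately before it is given is hard to place outside the personnel involved in administration.

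*Nurses are not given follow-up or data collection.* This is correct. The Intervention description gives compliance follow-up and timely recording of complications to trained volunteers, the Data collection section gives data to research volunteers, and Harms uses a standardized checklist. The exposure is therefore narrower than it might look. It lies in what passes between nurse and participant at dosing, and not in the recording itself.

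*The opened envelopes need not reveal the arm.* A reader might infer that the two researchers and the physicians learn the allocation. The document does not support this: the envelopes are described as independently encoded, the opened paper may carry only a code, and those researchers are not said to dose anyone. What stands is that the article does not say what the paper or the physicians' assignments show.

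*The analysis timing is consistent.* A reader might see a conflict between the Primary objective wording, "Upon trial conclusion and researcher and participant unblinding", and a statistician who stays blind. Both can hold. The first names researchers and participants, and the Blinding section already allows unblinding only once the data are collected and locked.

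**Conclusion.** The point holds on the nurse-preparation text alone. As written, the trial does not deliver the blinding that it declares for the staff who give the treatment, and the two statements on the source of the placebo disagree.

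The extent is all 50 planned controls, identifiable to any nurse who prepares their dose, over days 1–3. The effect on dose completion, symptom reporting and retention cannot be sized from the document.

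A reader might go further and conclude that the primary endpoint is read unblinded. The document does not support that, because the readers are separately blinded to group and to earlier scans.

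The conclusion assumes that nurses do prepare the placebo as the Intervention description says, and that no undisclosed procedure separates preparation from dosing. It takes as given that the two finished products match in appearance and taste.

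**What to change.** - Name one existing staff member, with backup, who takes no part in dosing, follow-up or outcome assessment. This person prepares the doses for both arms and passes them to the administering nurse in identical opaque containers that carry only participant number and day. Fresh daily preparation can be kept.
- State that the opened allocation document and the physicians' assignments show only a code.
- Make Trial design, Intervention description, Allocation and Blinding agree on who makes the placebo, who prepares each dose and who is blinded.
- If preparation cannot be separated from dosing, say that the preparing nurses are unblinded, and limit the blinding claim to participants, ultrasound readers, data collectors and the statistician.

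The Allocation section mentions an independent study team, but says only that it transmits assignments. Whether it has contact with participants or could prepare doses is not stated, so the plan should name the preparer explicitly.

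The cost is a small logistical one: separate preparation and labelled containers, at most 100 participants × 6 days = 600 if each dose has its own. No dose, schedule, endpoint or sample size changes.
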